## Methods

### Research Settings and Participants

#### Research Platforms

The proposed formative and intervention study will be conducted on Instagram, which is a popular social media platform for young US adults (71% use) [41,48] and home to many support groups for substance use prevention and reduction [49,50]. Recruitment sites will expand to Snapchat and Facebook (>65% use) [41], which are identified as useful recruitment sources for substance use prevention in young US adults [51,52]. As a pilot study for a cross-platform trial, the module prototypes will be developed based on Instagram features available on other platforms (eg, live streaming, voting polls, group chatting, and multimedia posting). Recent interventions developed on these features indicated efficacy on behavioral changes, including drug use [37,45,46,53-56].

#### Peer Leaders

The study will engage 4 peer leaders who are serving in recovery programs at substance use–related associations or communities for young adults (ie, Gamecock Recovery at the University of South Carolina). The study takes advantage of this model in various aspects, including recruitment and intervention development or delivery. Eligible leaders will be those who are (1) aged between 18 and 25 years, (2) formally trained as a recovery coach (>40 h), (3) have had successful recovery from opioid misuse or opioid use disorder, and (4) use social media (eg, Instagram, Facebook, and Snapchat) on a daily basis. The health psychologist and addiction treatment experts and doctoral-level clinical psychology trainees at the Integrated Care for Recovery (I-CaRe) Training Center at the University of South Carolina will provide training and ongoing support for the peer leaders. e-gift cards will be provided to compensate for their time (US $2 for each recruitment; US $30/h for intervention).

#### Participants and Recruitment

Participants for the formative study and intervention trial will be those who meet the following inclusion criteria: (1) aged between 18 and 25 years, (2) US residents, (3) engaged in NMUPO in the past 3 months, and (4) using Instagram at least 3 times a week in the past 3 months. NMUPO refers to the occurrence of the following behaviors (1 time or more): (1) taking a prescription opioid without a prescription, (2) taking more doses than prescribed, and (3) using opioid for a nonmedical reason (eg, getting high) [1-3]. Individuals will be excluded if they report (1) receiving substance use interventions in the past 3 months, (2) being diagnosed with SUD, or (3) not being proficient in English. We anticipate a total sample size of 100, with 30 for the formative study and 70 for the intervention trial.

The entire recruitment procedure is presented in Figure 2. Recruitment will be conducted using two strategies: (1) peer outreach and (2) advertising campaigns. For the peer outreach approach, peer leaders will distribute recruitment advertisements via online social networking (eg, posting advertisements on their social media accounts and inviting subscribers to repost the advertisements). Peers can also send direct invitations to young adults who they personally know to be eligible for the study. For advertising campaign approaches, we will target the accounts (on Instagram or Facebook) of colleges, local young adult communities (eg, trade unions), and substance use support groups. Upon approval from their group administrators, we will post advertisements in the groups. In addition, we will develop targeted advertising using Ads Manager (Meta Platforms, Inc) [57]. The advertisements will display research-relevant images, hashtags, and headings, which are tailored to engaging content for young adults. To ensure appropriateness, the advertisements will be reviewed by a community advisory board. The advertisements for aim 3 will be improved in line with formative research. The Ads Manager will also determine the range of the advertisement campaign in terms of age, time, and locations (ie, the United States). The designed advertisements will be delivered in various formats dependent on the platforms, such as linear posts within personal feeds on Instagram, news feeds on Facebook, and stories on Snapchat. To ensure representativeness, recruitment will be stratified based on key demographics (eg, gender, race or ethnicity, and education) in line with the latest US national data on NMUPO [58]. The advertisements will navigate potential participants to a web-based sign-up survey on REDCap (Research Electronic Data Capture; Vanderbilt University), which is a secured web-based platform monitored by the University of South Carolina. The prescreening survey will include questions in terms of age, past–3-month NMUPO (National Institute on Drug Abuse [NIDA]–Modified Alcohol, Smoking and Substance Involvement Screening Test [59]), US residency, use of social media, and SUD diagnosis or treatment history. Participants who are identified as eligible will provide their preferred contact method (eg, Zoom [Zoom Communications, Inc]) in the survey for a brief preinterview online meeting with the study team for a fraudulent screening. Such a screening will be conducted by checking for inconsistencies in their responses, requesting time-stamped screenshots to prove their locations, and asking for information (eg, brand names) of prescription opioids that they have been using. Eligible participants with no fraud responses will then be invited to complete web-based informed consent. Young adults enrolled in the study will be provided with instructions for interviews (aim 1) or intervention (aim 3).

Our recruitment approaches are considered feasible according to existing data. Feasibility research examined the advertising campaign approach on Facebook to reach young adults engaged in NMUPO, showing that it successfully recruited 689 participants over 2 weeks (91% past-year misuse) [35]. The US national data indicate that the majority of young people with NMUPO do not have SUDs (2801/3257, 85.9%) [60]. Previous substance use studies indicated retention rates of 75% to 93% among young adults reached by social media [46,53,61].

**Figure 2 figure2:**
[figure not shown]
CONSORT (Consolidated Standards of Reporting Trials) flowchart of the proposed study. EMA: ecological momentary assessment; IMB: information-motivation-behavioral skills; NMUPO: nonmedical use of prescription opioids; RCT: randomized controlled trial.

### Study Design and Procedures

#### Aim 1: Formative Study

Young adults who are social media users (eg, Instagram and Facebook) and indicate NMUPO will be invited to web-based 60-minute individual semistructured in-depth interviews. The interview guide will be based on the IMB model and aim to (1) identify NMUPO patterns (eg, drug classes and individual behaviors), (2) understand psychosocial factors contributing to reducing NMUPO, (3) extract vivid examples related to psychosocial content, (4) identify planning processes and coping skills facilitating the change, (5) assess the feasibility and acceptability of social media to manage NMUPO, and (6) review recruitment advertisements. This will provide the foundational knowledge and materials to develop specific content (eg, video and posts) for the intervention. The interviewers will be trained research assistants from the fields of psychology or public health. As suggested by the guideline of qualitative research [62], the sample size will be 30 young adults.

Interviews will be audio recorded, transcribed, and coded using a pragmatic approach. The framework analysis [63] will be performed via a deductive process, including five key steps: (1) familiarizing the data, (2) developing a coding scheme, (3) condensing and structuring the data, (4) rearranging the coded data and comparing patterns, and (5) mapping and interpretation [64]. A codebook will be developed based on step 2 as a guide for coding. Coding disagreements will be resolved through group discussion. Data analysis will be conducted on NVivo (version 11.0; Lumivero). Interrater reliability will be assessed throughout the coding process with a goal of ≥0.80 [65].

#### Aim 2: Intervention Development

##### Intervention Strategies

The intervention will apply various principles in psychotherapy. The intervention materials (texts, videos, and images) and activities will be developed using the findings from the formative study. To address particular factors in the IMB model, it will be based on peer support for behavioral change, motivational interviewing (MI) [66], cognitive behavioral therapy (CBT) [67], and solution-focused therapy (SFT) [68], which have been widely applied in substance use interventions [69-71]. Peer support is promising for facilitating social support and skill coaching [72]. MI is used to resolve cognitive ambivalence (eg, positive expectancies of substance use vs the benefits of making change), which is particularly beneficial for promoting motivation [73]. CBT is widely applied to distress management by reframing negative thoughts and facilitating adaptive coping [74]. SFT emphasizes a focus on problem-solving and is favorable for setting concrete goals (action planning) [75,76]. This content and these activities will be packed in different modules.

Incorporating inputs from peer leaders, the video content will follow a video prompting strategy [77]. Videos will feature peer leaders and involve breaking tutorials into steps, allowing young adults to learn and rehearse cognitive and behavioral skills in a sequential fashion. For example, guided by CBT, a peer leader may lead participants may lead participants to reflect on the context, thoughts, and consequences, related to their last experience of NMUPO, and then practice adaptive responses (eg, positive reframing and replacement behaviors). Video prompting has been effective for skill coaching in young adults [78].

##### Intervention Components

###### Overview

The proposed intervention components are guided by the IMB-based conceptual framework (Figure 1), with each component targeting specific factors derived from 3 psychosocial constructs (ie, information, motivation, and behavioral skills). As outlined in the framework, the pacing of intervention is structured to prioritize addressing information and motivation factors during the initial phases, while later sessions progressively promote behavioral skill training that contributes to psychological distress management and NMUPO reduction. Incorporating Instagram functions, the intervention platform is proposed to consist of four intervention modules, including (1) NMUPO knowledge module, (2) self-care module, (3) internet-based goal setting or monitoring module, and (4) peer support module (Figure 3). These are planned, and final content will be informed by or modified in line with the formative research. The research team will work closely with the community advisory board and peer leaders to ensure appropriate content and language. The intervention will last 12 weeks according to previous social media trials (typically 8-12 wk) [37,44,79-86]. Clinicians will review the intervention materials and ensure the scope is appropriate. Content will be prompted daily as suggested by the IMB model (eg, initially focus on information and motivation factors and gradually enhance the role of behavioral skills).

**Figure 3 figure3:**
[figure not shown]
Planned intervention modules and strategies. I-CaRe Training Center: Integrated Care for Recovery Training Center; IMB: information-motivation-behavioral skills; NMUPO: nonmedical use of prescription opioids; PI: principal investigator; WDC: Web Development & Communication.

###### NMUPO Knowledge Module

A self-paced psychoeducation module will be developed targeting information and motivation factors. This module will provide the latest information about prescription opioids (eg, illicit manufacture and the role of fentanyl, naloxone, and xylazine) and the harms of NMUPO, introduce the benefits of use reduction, and clarify misconceptions. Each component will display vivid stories drawn from the formative study and delivered via multiple formats, including images, videos, and text. Participants can react to the posts by leaving comments or by liking the posts. The majority of the content will be based on MI strategies (eg, ambivalence resolution). This media campaign strategy, combined with prevention education, has been identified as an essential approach for reducing NMUPO in young adults [25].

###### Self-Care Module

This module will provide tutorial materials on behavioral skills for managing psychological distress and identifying strengths to make changes. Material formats (videos, texts, and images), duration, and content will be determined by the findings from the formative study. For example, serial 3-minute tutorial videos will introduce CBT strategies for reframing negative thoughts (eg, “I’m a total failure”) and exploring intrapersonal or interpersonal strengths (eg, resilience). Tutorials will be step-by-step based, allowing participants to role-play and rehearse, presented with vivid examples extracted from the formative research (aim 1). Such a self-guided CBT component has proven effective in reducing psychiatric distress [87].

###### Internet-Based Goal Setting or Monitoring Module

This module aims to enhance action planning skills to reduce NMUPO. Specifically, it will assist young adults with setting personalized goals associated with NMUPO reduction and tracking progress toward meeting the goal. Web-based activities will be developed using SFT strategies. For example, the video will guide using scaling questions, which help participants identify their confidence levels to stop NMUPO and make a realistic plan based on it. Participants will then be instructed to explore barriers and their corresponding coping strategies for moving up the scale. Peer leaders will track their progress and provide support via online support group meetings. In addition, tutorials will instruct participants to set daily reminders or notifications on their devices (eg, mobile phone) to monitor the progress. This virtual self-monitoring has been a promising strategy to manage psychiatric distress and substance use [88].

##### Intervention Encouragement and Monitoring

Several strategies that are shown to be useful for enhancing engagement will be used [82,84,89-92]: (1) reminder notifications (via Instagram or emails); (2) prompt replies to participants’ messages; and (3) biweekly prize draws of US $25 gift cards for those who post, attend meetings, and reply on the panels. The intervention will be overseen by PI and a licensed clinical psychologist at the I-CaRe Training Center, under supervision from experts in addiction medicine and psychotherapy for SUD. They will provide preintervention training (eg, skills in MI or CBT techniques and findings from aim 1) and weekly guidance to peer leaders. They will also advise on referrals to link participants to licensed mental and behavioral health professionals in their states of residence if necessary. The doctoral-level psychology trainees at I-CaRe Training Center will support intervention delivery by (1) ensuring conversations are intervention related and banning inappropriate content; (2) promptly replying to participants’ comments; and (3) monitoring participants’ safety (eg, emotional reactions to the posts and in the online group meetings) and offering referrals for outside psychological services, if needed. They will also be responsible for reporting adverse events to the PI if observed.

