#### Aim 3: Intervention Feasibility and Preliminary Efficacy Evaluation Study

##### RCT Design

The intervention modules will be tested through an RCT design using mixed methods in 70 young adults who engage in NMUPO [93]. The primary purpose is to determine acceptability, usability, feasibility, and initial efficacy. Participants reached by peer leaders or advertisements on social media will be navigated to a screening survey on REDCap and scheduling a meeting with the research team for informed consent. Participants will be required to comply with the user safety agreement. Participants will be randomly assigned to the parallel intervention (35/70, 50%) or control group (35/70, 50%) using computer-generated random numbers. Participants are blinded to the randomized assignments. Intervention group will be guided to join Instagram peer-led private groups (n=10-15 each). Participants will be asked to provide their Instagram accounts to their assigned peer leaders for participating in intervention activities. Peer leaders will set up private and independent groups via their Instagram accounts and will send direct invitations to their assigned participants to join groups. Once group membership is confirmed, peer leaders will post intervention materials and lead group activities according to the plan as developed in aim 2. Private groups will synchronously deliver intervention packages over 12 weeks. To ensure confidentiality, participants will be assigned unique study IDs, which will be used for data collection and intervention activities. The intervention group will participate in data collection through multiple formats, including Instagram paradata, pre- and postintervention surveys, EMA surveys, and postintervention semistructured interviews.

The control group will not engage in any intervention activities but will complete the pre- and postintervention surveys.

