##### Web-Based Pre- and Postintervention Surveys

The web-based pre- and postintervention surveys will be developed and administered on REDCap [94] to measure demographic variables as well as psychosocial and behavioral factors outlined in the IMB-based conceptual framework. Factors include NMUPO behaviors (past–3-month NMUPO) and information- and motivation-related factors (ie, NMUPO knowledge, NMUPO risk perception, outcome expectancies, self-efficacy, psychological distress, resilience, and other substance use). Web-based surveys will be conducted among participants in both the intervention and control groups. Participants will receive survey links via inbox messages to the Instagram accounts they provide for the study. The preintervention survey will be sent 2 weeks before the intervention (baseline), and the postintervention survey will be sent in the week immediately following the intervention (12-week follow-up). The survey will be self-administered and take approximately 20 to 30 minutes to complete. If participants cannot complete the surveys at one time, they can save their responses, and the platform will generate a code that allows them to resume the survey within the same week. The survey will also provide forward and back buttons, allowing participants to review and change their responses before they submit their surveys. Study IDs and filling time will be collected for determining duplicate entries. e-gift cards will be provided for the completion of surveys (baseline and 12 weeks; US $30 each).

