##### Psychological Distress

Depression and anxiety symptoms in the past 2 weeks will be assessed using the Patient Health Questionnaire-9 [104] and Generalized Anxiety Disorder-7 [105], respectively. The Patient Health Questionnaire-9 is composed of 9 items asking the frequency of depressive mood experiences (eg, “feeling down, depressed, and hopeless”), while the Generalized Anxiety Disorder-7 comprises 7 items assessing the frequency of feelings of nervousness or worry (eg, “not being able to stop or control worrying”). Two scales have 4 response options ranging from 0 (not at all) to 4 (nearly every day). Sum scores for 2 scales will be generated, with higher scores indicating greater levels of depression or anxiety.

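### The only adverse-event capture described is staff observation during intervention delivery, with no equivalent for controls, so adverse-event counts could not be compared between arms

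*Protocol article*

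**What the plan says.** Under Intervention Encouragement and Monitoring, the Protocol article describes the staff role that carries adverse-event reporting. It opens "The doctoral-level psychology trainees at I-CaRe Training Center will support intervention delivery by" and goes on to list moderation of content, replies to comments, and safety monitoring with referral. The settings given as examples for safety monitoring are "eg, emotional reactions to the posts and in the online group meetings". The paragraph closes with the reporting duty: "They will also be responsible for reporting adverse events to the PI if observed".

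Under RCT Design, the intervention arm supplies data through several channels, "including Instagram paradata, pre- and postintervention surveys, EMA surveys, and postintervention semistructured interviews". For the other arm: "The control group will not engage in any intervention activities but will complete the pre- and postintervention surveys".

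Under Web-Based Pre- and Postintervention Surveys, the two arms share one instrument: "Web-based surveys will be conducted among participants in both the intervention and control groups". Besides past-3-month nonmedical opioid use, the listed content is "NMUPO knowledge, NMUPO risk perception, outcome expectancies, self-efficacy, psychological distress, resilience, and other substance use". The Measures section describes these scales one by one. For distress, for example: "Depression and anxiety symptoms in the past 2 weeks will be assessed using the Patient Health Questionnaire-9 [104] and Generalized Anxiety Disorder-7".

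**The concern.** The reporting duty is conditional on observation, and the people who hold it have a described role only in delivering the intervention. Controls are not in the groups or the meetings. Taken together, these statements give unequal ascertainment: some events seen in one arm, and no described means of recording any in the other.

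At stake is how the pilot's safety record can be read. The trial brings together young adults who misuse opioids in groups that discuss that use, and it is meant to support a larger trial. If events recorded this way were set out by arm, an excess in the intervention arm could come from ascertainment alone. Few events would not be reassuring either. A participant who stops posting and attending, possibly because of harm, is the one staff are least likely to see.

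**Working it through.** The Protocol article states no adverse-event rate, harm endpoint or safety sample size, so there is no planned figure to reproduce. The check sets the sections side by side and then sizes the effect under stated assumptions.

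**1. Could another described instrument record an adverse event?**
- Surveys, both arms: the listed measures are scales of opioid use, knowledge, outcome expectancies, risk perception, self-efficacy, distress, resilience and other substance use. None asks about a discrete event such as an overdose or a hospital admission.
- Ecological momentary assessment, intervention arm only: acceptability, usability and dose.
- Week-12 interviews, listed among the intervention arm's data sources: feasibility, usability, acceptability and reactions to content and assessments.
- Ethical Considerations, and the limitations in the Discussion: no adverse-event collection is described and the imbalance is not mentioned.

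**2. What can the common scales show?** Opioid use, distress and other substance use are measured the same way in both arms at baseline and 12 weeks, so a worsening can be compared without this bias. Two limits apply.
- The distress scales look back 2 weeks. A survey sent just after a 12-week intervention leaves roughly the first 12 − 2 = 10 weeks uncovered.
- Precision is low. The detectable standardized difference at 80% power and two-sided 5% is d = (1.96 + 0.84) × √(2/n). With n = 35 per arm, d = 0.67. With n = 26 (75% retention), d = 0.78.

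**3. Size of the ascertainment gap (illustration).** Inputs: n = 35 per arm, from the Protocol article. The true event rate (equal in both arms) and the share visible to staff are assumptions. Capture in controls by the described route is taken as 0.

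Expected records = n × rate × share visible. Chance of at least one true control event = 1 − (1 − rate)^35.

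| True rate, both arms | True events per arm | Recorded, intervention (25% / 50% / 100% visible) | Recorded, control | Chance of ≥1 true control event |
|---|---|---|---|---|
| 5% | 1.75 | 0.44 / 0.88 / 1.75 | 0 | 83.4% |
| 10% | 3.5 | 0.88 / 1.75 / 3.5 | 0 | 97.5% |
| 20% | 7.0 | 1.75 / 3.5 / 7.0 | 0 | over 99.9% |

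**4. What a common survey block would buy.** With zero events among m respondents, the one-sided 95% upper limit is 1 − 0.05^(1/m). The Power Analysis section cites retention of 75% to 93% in earlier trials.
- Full response, m = 35: 8.2%.
- 93% retention, 35 × 0.93 = 32.55, so m = 33: 8.7%.
- 75% retention, 35 × 0.75 = 26.25, so m = 26: 10.9%.

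These limits apply to respondents only.

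**The case against.** The strongest reply is that the adverse-event sentence assigns one duty to one staff group and does not say that this is the only route. The text is a journal article, the full aim 3 protocol is not shown, and the Results section says it goes to the ethics board only in early 2027. The survey list is not a full inventory either: the Abstract names intention and coping strategies as secondary outcomes, and neither is in the list of survey factors. No by-arm table of adverse events is planned, and the primary outcomes are feasibility, usability and acceptability.

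Much of this stands, and it rules out several stronger readings that a reader might draw.
- That controls have no way to report an event. The document does not say so; it describes none.
- That harms cannot be compared at all. Distress, opioid use and other substance use are measured identically in both arms.
- That observation is limited to Instagram posts. It includes weekly live video meetings, and staff also have direct contact at the week-12 interview.
- That the trial will publish a biased by-arm comparison. None is stated.

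The reply does not remove the core point. The article is not silent on adverse events. It states a capture rule, and that rule is passive and tied to activity that only one arm undertakes. Applied as written, it gives unequal ascertainment, and no described instrument corrects this.

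**Conclusion.** The point holds in limited form. The only adverse-event capture described is passive observation during delivery of the intervention. No equivalent is described for controls, and the listed survey measures contain no discrete adverse-event items. Counts of adverse events would be ascertained unequally and could not be compared between arms. Deterioration on the common scales can be compared, though only large differences (about 0.67 to 0.78 standard deviations) would be detectable with 80% power.

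The illustrative 1.75 against 0 rests on an assumed 10% event rate and 50% visibility, neither of which comes from the document. The direction does not depend on those values: with no capture in controls, any visible event tilts the count against the intervention. No sample size, power or alpha figure in the plan is affected. The change is worth making because it costs little and the aim 3 protocol has not yet gone to the ethics board.

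**What to change.** - Add the same short adverse-event block to the 12-week REDCap survey in both arms, asking about discrete events since baseline (for example overdose, emergency visit, hospital admission, self-harm).
- Report those events by arm, with the number of respondents as the denominator and an exact confidence limit. State that the survey misses participants who drop out, who may include those most seriously affected.
- Report staff-observed events separately and descriptively, as monitoring of the intervention arm only.
- If the full aim 3 protocol already has a route for controls, state it and confirm that it is the same in both arms.

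Cost: a few survey items, one table and a slightly longer questionnaire. Serious self-reports would also need routing to the referral process that the plan already describes.
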